**Baseline only:**	
1	Demographic questions: including age, race, marital status, occupation, and education
2	Duration of hypertension
3	Past medical history
4	Contraindications to anti-hypertensives
5	Short orientation memory test [15]
6	Height
7	Joint pain questionnaire [16]
Baseline and follow-up:	
1	New medical history (in last 6/12 months)
2	Blood pressure (sitting plus standing at baseline)
3	Current anti-hypertensive medications
4	Weight
5	Symptom section of the IPQ [17]
6	Partners in health scale [18]
7	Short-form of the State-Trait Anxiety Inventory [19]
8	EQ-5D [20]
9	Use of complementary and alternative medicine and self-tests [21]
10	BP measurement preference
11	Attitudes to health and healthcare [22]
Lifestyle diaries	
1	Simple lifestyle indicator questionnaire (SLIQ) [23]
2	The dietary quality score [24]
3	Self-efficacy (adapted diabetes self-efficacy scale) [25]

Patients will be asked to attend two follow-up clinics at 6- and 12-months post-randomisation. Each clinic will be timetabled for no more than one hour, during which patients will have their BP and weight measured by the research team and will be asked to complete a questionnaire similar to the one completed at baseline. At the 12 month follow up, participants will also be given a blank postcard and asked to write a few sentences about their experience of the trial. Additionally, the research team will check that patients in the intervention arm are using the blood pressure monitors correctly. Flow through the trial is summarised in Figure 1.

**Figure 1 F1:**
[figure not shown]
Flow through the trial.

### Sample size considerations

A sample size of 243 people per group is required for 90% power assuming a standard deviation of 17 mmHg and a difference of at least 5 mmHg between intervention and control groups. This represents a clinically significant decrease in BP and is in line with the reduction observed in TASMINH2 and would result in around 20% reduction in stroke risk and 10% coronary heart disease risk. Based on the follow-up in TASMINH and TASMINH2 self-monitoring trials, a 10% drop out rate during follow-up is assumed, meaning a sample of 270 per group will need to be randomised, a total of 540 patients altogether. Should the drop-out rate be higher than TASMINH2, for instance 20%, the study would have more than 85% power.

### Recruitment

Patients will be recruited over an eight month period. Based on practice-based pilot searches, it is estimated that in a practice with an average size of 6000 patients, 2.5% will be eligible for invitation. Previous experience from the TASMINH2 trial suggests that approximately 30% of invited patients will attend baseline clinics, and of these 50% will be eligible [8]. A minimum of 25 practices will be needed in order to recruit the required number of participants (approximately 22 patients per practice being randomised) but many more will be available if necessary.

### Statistical analysis

The primary analysis will include all available participants, i.e. all of those with complete data from follow-up, and will be performed at the end of the trial after all data has been collected. A mixed model analysis will be used to examine differences between intervention and control systolic BP at twelve months, adjusting for practice (as a random effect), baseline BP, gender, and high risk group. Planned sub group analyses will be of older vs younger (65 as threshold), males vs females, better controlled at baseline vs worse controlled at baseline (threshold 145 systolic), the different risk groups and deprivation. Sensitivity analyses will examine the potential effect of missing data. These will include multiple imputation, replacement of missing data by the most recent previous data or by the mean of the series. Any deviation from the original statistical plan will be described in the final report and publications.

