## Methods/Design

### Study aims, research questions, and outcomes

The primary aim of TASMIN-SR is to compare self-management with usual care in the control of hypertension in patients with stroke and other at-risk conditions.

The trial has four main research questions:

1. Does self-management of blood pressure result in better control of blood pressure in people with stroke and other at-risk conditions compared to usual care?

2. Is self-management of blood pressure in people with stroke and other at-risk conditions achievable in routine practice and is it acceptable to patients?

3. What is the relationship between self-management of blood pressure, self-efficacy, lifestyle behaviours, patients’ attitude to health and health care and use of other self-care strategies in people with stroke and other at-risk conditions?

4. Is self-management of blood pressure in people with stroke and other at-risk conditions cost effective?

The primary outcome of the trial will be the difference in office systolic blood pressure (mmHg) at 12-month follow-up between intervention and control adjusted for baseline blood pressure and co-variates. Secondary outcomes (also adjusted for baseline and co-variates) will include:

–  Difference in office SBP at 6-month follow-up between intervention and control

–  Difference in office DBP at 6 and 12-month follow-up between intervention and control

–  Percentage time in target BP range

–  Difference in pulse rate

–  Difference in self-management self-efficacy

–  Difference in lifestyle behaviours

–  Difference in health-related quality of life

–  Difference in BP measurement preference

–  Difference in anxiety

–  Difference in attitudes to health and healthcare

–  Difference in use of other self-management strategies

–  Reasons for non-participation

–  Adverse events (including cardiovascular events and death)

–  In addition there will be a qualitative analysis and health economic modelling.

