### Study population

The study population will comprise people with stroke/TIA, diabetes, CKD3, CABG, MI or angina, with poorly controlled hypertension managed in primary care. Eligibility criteria will be age above 35, have had a diagnosis of stroke/TIA, diabetes, CKD3, MI, angina, or CABG, and clinic blood pressure greater than 130/80. Exclusion criteria will be inability to self-monitor (such as dementia or score of >10 on the short orientation memory concentration test), postural hypotension (systolic BP drop > 20 mmHg), prescribed more than three anti-hypertensive medications, taking part in a current BP study or previously having taken part in TASMINH2 [8], terminal disease, pregnant, BP not managed by GP, and acute cardiovascular event in the previous three months.

Eligible patients will be identified from general practices via the UK Primary Care Research Network. Trained practice nurses will identify potentially eligible patients by searching practice-based registers for patients having a Read Code of stroke/TIA, diabetes, CKD3, Angina, CABG, or MI and whose last systolic BP measurement was greater than 145 mmHg (BP readings are often lower when measured by research teams, so a higher BP at invitation increases the likelihood of BP readings falling within the suitable range [13].) GPs will be asked to check the generated lists and remove patients who have a terminal illness, are pregnant, or who are thought to be unsuitable for the study.

Participants who withdraw will not be replaced, but asked if they are prepared to continue to attend follow-up clinics.

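### The primary analysis is a complete-case model of 12-month SBP that leaves out the 6-month SBP, so it can be biased, chiefly if the link between 6-month SBP and dropout differs by arm

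*Protocol article*

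**What the plan says.** Under Statistical analysis, the protocol article defines the analysis set: "The primary analysis will include all available participants, i.e. all of those with complete data from follow-up". It then gives the model: "A mixed model analysis will be used to examine differences between intervention and control systolic BP at twelve months". The terms in that model are set out next: "adjusting for practice (as a random effect), baseline BP, gender, and high risk group". No person-level random effect and no 6-month SBP is named.

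The 6-month SBP will nevertheless be collected. Under Study clinics and flow through study: "Patients will be asked to attend two follow-up clinics at 6- and 12-months post-randomisation", with the research team measuring BP at both. Study aims, research questions, and outcomes lists it as a secondary outcome: "Difference in office SBP at 6-month follow-up between intervention and control".

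Two provisions address missing data. Statistical analysis adds: "Sensitivity analyses will examine the potential effect of missing data". It then lists three methods for this purpose: "These will include multiple imputation, replacement of missing data by the most recent previous data or by the mean of the series". Study population says: "Participants who withdraw will not be replaced, but asked if they are prepared to continue to attend follow-up clinics".

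Sample size considerations assumes 10% dropout and also considers 20%.

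**The concern.** A model of 12-month SBP in people who have that value is unbiased only if, given arm and the adjusted covariates, being missing at 12 months is unrelated to what the 12-month SBP would have been. The 6-month SBP is a post-randomisation reading taken by the same team, and it predicts 12-month SBP beyond baseline. If people leave after 6 months partly because of how their blood pressure is going, the condition fails, and the model has no means of correcting for it.

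What matters most is whether this selection differs between arms. The trial is unblinded. Only the self-management arm has training sessions, monthly measurement weeks, forms to return and self-titration, while the control arm has routine care. A person whose readings stay high may therefore have a different reason to stop attending in one arm than in the other.

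The stake is the headline 12-month difference, and with it the trial-based cost per 1 mmHg reduction described under Economic analysis. The direction is not known in advance. Losing people with high 6-month SBP from self-management exaggerates the benefit; losing them from usual care understates it.

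**Working it through.** **1. The plan's own figures.** Inputs from Sample size considerations: difference 5 mmHg, SD 17 mmHg, power 90%. The article does not state the significance level; two-sided 5% is assumed because it reproduces the figure (one-sided 5% gives 198).

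- n per arm = 2 × 17² × (1.960 + 1.282)² / 5² = 243.
- With 10% dropout: 243 / 0.90 = 270 per arm, 540 in all.
- With 20% dropout: 270 × 0.80 = 216 per arm, power 86.4%, consistent with the stated value above 85%.

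These figures reproduce, so the point is not about a wrong number.

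**2. Size of the bias when dropout depends on 6-month SBP in one arm only.** The documents give no correlations and no dropout mechanism, so the following are assumptions: SD 17 at each visit; correlations (baseline–6 months, baseline–12 months, 6–12 months) of (0.3, 0.3, 0.5), (0.5, 0.4, 0.6) or (0.5, 0.5, 0.7); logistic dropout after 6 months with odds ratio OR per SD of 6-month SBP.

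Let p be an individual's dropout probability and d its mean. Among those retained in the affected arm, mean 6-month SBP is lower by

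shift (in SD) = ln(OR) × E[p(1 − p)] / (1 − d).

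After adjustment for baseline, the 12-month mean in that arm moves by about

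bias = 17 × (r(6,12) − r(0,6) × r(0,12)) × shift.

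For OR 2 and correlations (0.5, 0.4, 0.6):

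- d = 10%: shift = 0.693 × 0.0860 / 0.90 = 0.066; bias = 17 × 0.40 × 0.066 = 0.45 mmHg.
- d = 20%: shift = 0.693 × 0.1487 / 0.80 = 0.129; bias = 17 × 0.40 × 0.129 = 0.88 mmHg.

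Over the three correlation sets (absolute bias, mmHg):

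| Dependence, one arm only | 10% dropout | 20% dropout |
|---|---|---|
| OR 1.25 | 0.15–0.17 | 0.30–0.34 |
| OR 1.5 | 0.27–0.31 | 0.54–0.60 |
| OR 2 | 0.45–0.51 | 0.88–0.99 |
| OR 2, half the loss before 6 months and unrelated to SBP | 0.24–0.27 | 0.50–0.56 |

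**3. Check by simulation.** With 800,000 per arm, true differences of −4 mmHg at 6 months and −5 at 12, OR 2 and the same correlation sets:

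| Mechanism | Complete-case bias, 10% dropout | Complete-case bias, 20% dropout |
|---|---|---|
| Unrelated to 6-month SBP | about 0 | about 0 |
| Same relation in both arms | 0.04–0.06 | 0.07–0.12 |
| One arm only | 0.46–0.51 | 0.88–1.02 |

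The sign in the last row depends on the arm: with 10% dropout, dependence in self-management only gave about −5.5, and in usual care only about −4.5. Imputing missing 12-month values within arm from baseline and 6-month SBP returned −4.96 to −5.05 in every scenario.

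**4. Consequence for power.** Power = Φ(difference / (17 × √(2/n)) − 1.96).

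- 10% dropout, n = 243, shift of 0.5 towards the null: 4.5 / 1.542 − 1.96 = 0.96, power 83% instead of 90%.
- 20% dropout, n = 216, shift of 1.0 towards the null: 4.0 / 1.636 − 1.96 = 0.49, power 69% instead of 86%.

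A shift away from the null would instead overstate the benefit by the same amount.

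**The case against.** The strongest reply is that the plan already deals with missing data. It schedules multiple imputation, which can include 6-month SBP, and asks people who withdraw to keep attending. The article condenses a fuller protocol, so the unstated imputation model is no fault. A baseline-adjusted model of observed 12-month values, backed by imputation, is also a recognised approach. All of this stands, and it rules out any inference that missing data are ignored. But a sensitivity analysis does not change the estimate that will be reported as primary. The other two listed methods replace each missing reading with a single value, which needs stronger assumptions and understates uncertainty.

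The size is also modest. The 95% confidence interval half-width at 243 per arm is 1.96 × 17 × √(2/243) = 3.0 mmHg. Weaker dependence, or loss before 6 months, brings the bias at 10% dropout down to roughly 0.15 to 0.3 mmHg. That stands too, and is why the range is given rather than one figure. Bias, however, does not shrink with sample size as random error does.

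Three stronger readings are tempting and are not supported:

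- **That any dropout related to 6-month SBP biases the result.** With the same relation in both arms the bias is about 0.1 mmHg or less. The documents give no evidence of a difference between arms; they assume a single dropout rate.
- **That someone with a 12-month SBP who missed the 6-month clinic is excluded.** The words on complete follow-up data permit this, but they gloss all available participants, and the outcome is at 12 months. It is an ambiguity of wording only.
- **That the bias would reach 2 mmHg.** That takes opposite relations in the two arms at 20% dropout (1.7 to 2.0 mmHg in the same simulation), which nothing in the article suggests.

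Conversely, the term mixed model cannot be taken to mean a repeated-measures model here, since the outcome is at 12 months and the only random effect named is practice.

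**Conclusion.** The point holds in a limited form. The stated primary analysis is complete-case, omits the 6-month SBP, and so drops participants seen at 6 but not at 12 months. It can bias the primary estimate, mainly if dropout depends on 6-month SBP differently in the two arms. That is plausible from the design but not shown by the documents.

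The bias is about 0.1 to 0.5 mmHg at 10% dropout and up to about 0.9 to 1.0 mmHg at 20%, that is, up to one tenth and one fifth of the 5 mmHg design difference. The range rests on the assumed SD, correlations and odds ratios (1.25 to 2 per SD, one arm only). The upper figures also need all the loss to occur after 6 months. The plan is workable as written, but a better primary analysis is available from data the trial already collects.

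**What to change.** Make the primary analysis a repeated-measures linear mixed model of 6- and 12-month office SBP in all randomised participants with at least one follow-up SBP, analysed as allocated. Include arm-by-time, baseline SBP-by-time, gender and high risk group, an unstructured within-person covariance and a random practice effect. The 12-month contrast remains the primary estimate, and the same model supplies the 6-month secondary outcome. Multiple imputation including 6-month SBP would be an acceptable alternative primary analysis.

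Move the complete-case model to the sensitivity analyses. Replace the phrase requiring complete follow-up data with wording that cannot exclude anyone who has a 12-month SBP.

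The cost is a change of wording and a slightly more complex model, with no new visits or data and no change to the sample size. Two limits remain. The model still assumes missing at random, so dropout that depends on the unobserved 12-month SBP still needs sensitivity analysis. People lost before 6 months gain nothing from it.

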### Randomisation

Patients will be randomised to either usual care or self-management using an internet based system with telephone backup. Minimisation will be used to take into account practice, gender, age, high risk group (CVD, diabetes, CKD3, CHD) and baseline BP.

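### Age is a minimisation factor but the only one missing from the primary model's covariates; adding it is a small, free improvement

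*Protocol article*

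**What the plan says.** The Randomisation section states: "Minimisation will be used to take into account practice, gender, age, high risk group (CVD, diabetes, CKD3, CHD) and baseline BP". The Statistical analysis section specifies a mixed model for systolic BP at twelve months, "adjusting for practice (as a random effect), baseline BP, gender, and high risk group". Side by side:

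| Factor | Used in minimisation | Named in primary model |
|---|---|---|
| Practice | yes | yes (random effect) |
| Baseline BP | yes | yes |
| Gender | yes | yes |
| High risk group | yes | yes |
| Age | yes | **no** |

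The section on study aims and outcomes defines the primary outcome as the difference "between intervention and control adjusted for baseline blood pressure and co-variates". It does not name the covariates, and it applies the same adjustment to the secondary outcomes. In the analysis plan, age appears only as a subgroup variable: "Planned sub group analyses will be of older vs younger (65 as threshold". Table 1 lists age among the baseline data.

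**The concern.** When allocation is balanced on a factor that predicts the outcome, the treatment estimate varies less from trial to trial than it would under simple randomisation. A model that contains the factor reflects this. A model that omits it leaves the factor's variation in the residual, so its standard error is too large and its test rejects too rarely under the null. The usual rule is therefore to carry the balancing factors into the primary model.

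This plan does so for four factors out of five, including practice as a random effect. The pattern looks like a model meant to mirror the minimisation, with one item dropped. What is at stake is some precision in the main result and agreement between the design and the analysis.

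**Working it through.** **1. Reproduce the plan's own figure.** Inputs from the Sample size considerations section: SD 17 mmHg, difference 5 mmHg, 90% power. Alpha is not stated; two-sided 0.05 is assumed because it reproduces the result (one-sided 0.05 gives 198).

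- n per group = 2 × (1.960 + 1.282)² × 17² / 5² = 243, as stated.
- With 10% dropout: 243 / 0.90 = 270 per group, 540 in total, as stated.
- With 20% dropout: 270 × 0.80 = 216 per group, power 86.4%, consistent with the claim of more than 85%.

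The sample size stands and this point does not touch it.

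**2. Set up the comparison.** Let r be the partial correlation of age with 12-month systolic BP, given the other model covariates. The protocol does not give it, so a range of 0 to 0.3 is assumed. Take 17 mmHg as the residual SD without age, 243 per group, and age balanced between arms.

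- Reported SE without age: 17 × √(2/243) = 1.542; half-width 1.96 × 1.542 = 3.02 mmHg.
- SE with age: 1.542 × √(1 − r²). With age balanced, this is also the true SE of the estimate from the model without age.
- Excess width: 1/√(1 − r²) − 1. This ratio does not depend on the SD or on n.
- Type I error without age: 2 × [1 − Φ(1.96/√(1 − r²))].
- Power with age: Φ(5/SE − 1.96). Power without age: Φ((5 − 3.023)/SE). SE in both is the SE with age.

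**3. Put the numbers in.** For r = 0.2, SE = 1.542 × √0.96 = 1.511. Half-width = 2.96. Excess = 2.1%. Type I error = 2 × [1 − Φ(2.000)] = 0.0455. Power with age = Φ(3.309 − 1.96) = 91.1%; without age = Φ(1.977/1.511) = 90.5%.

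| Assumed r | Half-width without age | Half-width with age | Excess width | Type I error without age | Power with / without age |
|---|---|---|---|---|---|
| 0 | 3.02 | 3.02 | 0% | 0.0500 | 90.0 / 90.0% |
| 0.1 | 3.02 | 3.01 | 0.5% | 0.0489 | 90.3 / 90.1% |
| 0.2 | 3.02 | 2.96 | 2.1% | 0.0455 | 91.1 / 90.5% |
| 0.3 | 3.02 | 2.88 | 4.8% | 0.0399 | 92.5 / 91.1% |

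**4. Check by simulation.** Five-factor minimisation of 486 patients in 25 practices was simulated 1,200 times per value of r, with age balanced in two categories. Mean half-widths without and with age were 3.046 and 3.032 (r = 0.1), 3.038 and 2.979 (r = 0.2), and 3.045 and 2.907 (r = 0.3). The excess is 0.4%, 2.0% and 4.7%, in agreement with the table. The simulated rejection rates carry a Monte Carlo error of about 0.006 and do not separate the two models, so the analytic type I errors are used.

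**5. Allow for coarser balance.** The table assumes perfect balance on age, whereas minimisation on age categories balances it only in part. In a separate simulation (540 patients; minimisation cut-points of 65 years and 145 mmHg assumed; age explaining 10% of residual variance), the reported SE without age was 1.292, its actual SE 1.263, and the SE with age 1.226. Uncredited balance is then (1.292 − 1.263)/(1.292 − 1.226) = 0.029/0.066 = 44% of the gap. The rest is the ordinary gain from adjusting for a predictor. Type I error without age is 2 × [1 − Φ(1.96 × 1.292/1.263)] = 0.045. Scaled to a nominal 90%, power without age is Φ(1.282 × 1.292/1.263) = 90.5%, and with age Φ(3.242 × 1.292/1.226 − 1.96) = 92.7%. Coarser balance thus means less conservatism and a slightly larger power difference, 2.2 points here.

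**The case against.** The strongest case is that nothing important depends on this. A reader might infer that the primary test is invalid, the estimate biased or the trial underpowered. The protocol supports none of these: omitting a balanced covariate does not inflate type I error, complete follow-up leaves no bias, and power stays at or above 90% in every row of the table. A reader might also take wider intervals as a fact. They are conditional: if age adds nothing beyond baseline BP and the other covariates, the loss is zero, and the protocol gives no figure to exclude that. This stands, and it sets the priority.

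It is also tempting to argue that age must be in the primary model because it defines a subgroup. That does not follow. The subgroup analysis would carry its own age term, and deprivation is likewise a planned subgroup variable without needing to be a primary covariate.

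A further defence is that a condensed article leaves such detail to a fuller plan, or that the unnamed covariates in the outcomes section include age. This does not stand: the Statistical analysis section lists the covariates by name.

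On the other side, the primary analysis uses only participants with follow-up data, while minimisation balances age among all those randomised. If dropout depended on age and differed between arms, that balance could be lost. The protocol does not say whether this is likely, so it is a supporting reason only.

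**Conclusion.** The mismatch is real: age is the one minimisation factor absent from the named primary-model covariates, and no reason is given. Its effect is zero to small and cannot be fixed from the protocol. Over an assumed partial correlation of 0 to 0.3, the interval is at most 4.8% too wide, or about 0.14 mmHg on a half-width of 3.02 mmHg. The power forgone is at most about 1.4 points under close balance on age, or about 2 points if the balance is coarse and age explains 10% of residual variance. Up to a correlation of 0.2 the widening is about 2% or less. These sizes rest on the assumed correlation, two-sided alpha of 0.05, a residual SD of 17 mmHg and 243 analysed per group. This is a minor point, worth acting on because it aligns the analysis with the design at no cost.

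**What to change.** In the Statistical analysis section, add age to the list so that the model adjusts for practice (random effect), baseline BP, age, gender and high risk group. Entering age as a continuous term is preferable, though this is a modelling choice. If age was left out on purpose, state why. The secondary outcomes then take the same covariates through the outcomes section, so no second edit is needed there.

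The cost is one added term in one sentence. Age is already recorded at baseline and is needed for the minimisation, and the sample size is unchanged. It is better done before analysis, because the protocol commits to reporting departures from the planned analysis and a later addition would have to be declared as one.

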### Economic analysis

The economic analysis will be in two parts. The first part is a cost-effectiveness analysis conducted alongside the randomised clinical trial (trial-based analysis). An economic evaluation will compare the strategy of self-management of blood pressure in at-risk patients to the strategy of usual care. Primary outcome will be expressed in terms of the cost per additional 1 mm Hg reduction in office SBP from baseline to 12 months. Use of utility-based outcomes (EQ-5D) will allow a secondary outcome to be the cost per quality-adjusted life year (QALY) gained over the same 12 months period. The results for both outcomes will be expressed in terms of incremental cost-effectiveness ratios (ICERs). NHS resource use will include hospital and GP consultations, medications, referrals, equipment and training. Intervention costs, including equipment and training, will be collected by the research team. All other resource use data will be collected from practice computer systems by the research team at follow up visits. Cost data will be derived from sources such as the British National Formulary (BNF), the National Schedule for Reference Costs and the Unit Costs of Health and Social Care (PSSRU) [26].

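### Carrying the last value forward and using the mean of the series are biased checks on missing 12-month SBP, even when drop-out is random and the primary analysis is unbiased

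*Protocol article*

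**What the plan says.** The Statistical analysis section bases the primary analysis on participants with complete follow-up data. It is a mixed model for 12-month systolic BP with practice as a random effect and with baseline BP, gender and high risk group as covariates. Six-month SBP is not among the stated terms. Sensitivity analyses for missing data follow: "These will include multiple imputation, replacement of missing data by the most recent previous data or by the mean of the series".

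The section on study clinics and flow sets the measurement schedule: "Patients will be asked to attend two follow-up clinics at 6- and 12-months post-randomisation". With the baseline clinic, that makes at most two study-clinic readings before the endpoint.

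The Sample size section plans for 10% drop-out and also considers 20%.

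**The concern.** A sensitivity analysis should show what happens to the result under a plausible alternative account of the missing values. The two single imputations instead rest on an account that this design makes implausible.

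BP can be expected to fall after baseline in both arms. Entry needs a clinic BP above 130/80, and invitation needs a last systolic reading above 145. Both arms are also asked to book a BP check with the study GP, with a medication review in usual care and a titration plan in self-management. A baseline reading is therefore a poor stand-in for a 12-month reading. Unequal loss is also plausible: the trial is unblinded, and only self-management brings training sessions and monthly readings with forms.

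At stake is the reading of the robustness section of the trial report. These two analyses could seem to weaken a valid primary result, or to strengthen it, purely because of how the gaps were filled.

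**Working it through.** **The plan's own figures.** The inputs are "assuming a standard deviation of 17 mmHg" and "a difference of at least 5 mmHg between intervention and control groups". Alpha is not stated; I assume 0.05 two-sided. This gives 243 per group at 90% power, as printed. 243/0.90 = 270 per group, also as printed. At 20% drop-out, 216 per group gives 86.4% power, consistent with the stated figure of more than 85%. None of these figures is in dispute.

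**Assumptions the article does not supply.** Drop-out is completely random, and half of drop-outs are lost before 6 months. Usual care falls by F = 10 mmHg, fully reached by 6 months. The treatment difference is 4 mmHg at 6 months and 5 mmHg at 12 months. Self-management therefore falls by 14 and then 15 mmHg. I read the series as the participant's own readings.

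**Formula.** With random drop-out and arms equal at baseline on average, the expected adjusted difference is the difference in mean change. For an arm with missing fraction m:

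- last value: mean fall = (1 - m) × fall at 12 months + (m/2) × fall at 6 months + (m/2) × 0
- mean of series: the same, with half the 6-month fall, because baseline and 6 months are averaged

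The mean falls by arm are:

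| Arm, missing | Last value | Mean of series |
|---|---|---|
| Usual care, 10% | 9.0 + 0.5 = 9.5 | 9.0 + 0.25 = 9.25 |
| Usual care, 20% | 8.0 + 1.0 = 9.0 | 8.0 + 0.5 = 8.5 |
| Self-management, 10% | 13.5 + 0.7 = 14.2 | 13.5 + 0.35 = 13.85 |
| Self-management, 20% | 12.0 + 1.4 = 13.4 | 12.0 + 0.7 = 12.7 |

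Subtracting gives the difference (true value -5):

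| Drop-out, usual care / self-management | Last value | Mean of series |
|---|---|---|
| 10% / 10% | -4.7 | -4.6 |
| 20% / 20% | -4.4 | -4.2 |
| 10% / 20% | -3.9 | -3.45 |
| 20% / 10% | -5.2 | -5.35 |

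Simulated trials (270 per arm, SD 17, assumed correlations between visits, analysis adjusted for baseline) agree to within about 0.1 mmHg, and complete cases stay at about -5.0. The correlations affect the standard errors, not these averages.

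**Range over the assumptions.**
- With F = 5 and 20% / 10% loss, the last value gives (9.0 + 0.45) - (4.0 + 0.5) = 4.95 and the mean of series (9.0 + 0.225) - (4.0 + 0.25) = 4.975. The bias almost vanishes.
- With equal loss F cancels. What matters is then the share of drop-outs seen at 6 months and the 6-month effect. Letting that share run from none to all, and the 6-month effect from 3 to 5 mmHg, at 10% missing the last value gives 4.5 to 5.0 and the mean of series 4.5 to 4.75. At 20% the ranges are 4.0 to 5.0 and 4.0 to 4.5.

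**Standard errors.** In simulation the model-based standard errors of the two single-imputation analyses (1.30 to 1.34) match the actual spread of their estimates (1.31 to 1.37).

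**The case against.** The strongest reply is that little turns on this. The primary analysis does not use these methods, and multiple imputation, a sound check under missing at random, is named first. At the planned 10% equal drop-out the bias is about 0.3 to 0.5 mmHg. Under the assumed set-up, last value carried forward then reaches significance as often as complete cases (94% for both, and 91% for both at 20% equal drop-out). Withdrawers are also asked to keep attending follow-up clinics, so stopping self-management need not mean a missing endpoint. All of this stands and limits the severity. It does not make the two named methods good checks.

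Four stronger readings are tempting, and the document does not support them.

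- A reader might infer that the standard errors are too small because filled-in values count as observed. They are smaller than the complete-case standard errors, but those belong to a different estimator. Each filled-in value comes from that patient's own readings, and the standard error matches the estimator's own spread. The fault is bias.
- A reader might infer that every drop-out is assigned no change, or that the effect always shrinks. Participants seen at 6 months contribute a post-treatment reading, and the bias reverses or nearly vanishes when usual care loses more.
- A reader might infer that robustness cannot be shown at all, or that leaving out a missing-not-at-random analysis is an error. The list is worded as open, and such an analysis is commonly left to the statistical analysis plan, which is not shown. Carrying a high baseline forward is itself a crude, ungraded departure from missing at random.
- A reader might infer that practice-recorded BP is available to inform the imputation. The Economic analysis section says "All other resource use data will be collected from practice computer systems by the research team at follow up visits", but that concerns resource use and does not mention BP.

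**Conclusion.** The point holds in limited form. The article commits to two single-imputation analyses that are biased for the 12-month difference under random drop-out, when the complete-case primary analysis is not. The bias is about 0.3 to 0.5 mmHg at 10% equal loss and about 0.6 to 0.8 at 20% equal loss. It is about 1.1 to 1.5 mmHg towards no effect if self-management loses 20% against 10%, and about 0.2 to 0.3 the other way if usual care does. These sizes rest on the assumed falls, 6-month effect and timing of loss, none of which the article gives. Severity is minor to moderate: the primary result is untouched and a better method is already planned beside these two.

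**What to change.** Drop the two single imputations, or demote them to a clearly labelled supplementary table. Make multiple imputation the main missing-data check. Run it separately by arm, with baseline SBP, 6-month SBP and the minimisation factors (practice, gender, age, high risk group, baseline BP) in the imputation model.

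In place of the two single imputations, add a graded delta-adjusted version. For example, raise imputed 12-month SBP by 0 to 10 mmHg, in both arms and in self-management only, and report the shift at which the conclusion changes.

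A rough guide to what this would show, for an observed difference of 5 mmHg with the shift in self-management only: the tipping shift is (5 - 1.96 × SE)/m, with SE = 17 × sqrt(2/n) and n the number observed per arm.
- At 20% missing: n = 216, SE = 1.64, tipping shift about 9 mmHg.
- At 10% missing: n = 243, SE = 1.54, tipping shift about 20 mmHg. This lies outside the example range, so the report would say that the conclusion did not change within it.

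The cost is a change of wording and a little extra programming. No new data are needed.
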